## Abstract

**Introduction:**

Integrated emergency care systems are essential for achieving universal health coverage and managing time-sensitive conditions. In India, emergency care remains fragmented, with limited resources and coordination across healthcare tiers. The INDIA-EMS study aims to develop and evaluate a patient-centric, high-quality integrated emergency care model in diverse Indian districts.

**Methodology:**

The proposed implementation research is designed as a mixed methods study to be conducted over a 3-year period in selected districts of the states of Punjab, Gujarat, Madhya Pradesh, Odisha and Puducherry. The public/private medical college hospital/ tertiary care hospital in the district will serve as a hub and primary health care services as spokes. The health facilities will be graded according to the availability of resources for their readiness and preparedness to provide care for handling a particular emergency condition. The steps to build and implement the model are: 1. a gap analysis related to emergency care at both pre-hospital and health facility level; 2. a community-based survey in a sample of 30,000 in 5 districts for EMD burden estimates and health-seeking behaviour at baseline and endline; 3. use a consolidated framework for implementation research to develop, optimise and implement hub and spoke model through three cycles of iterative processes; and; 4.evaluation for feasibility, acceptability, cost, effectiveness and coverage.

**Discussion:**

A high-quality patient-centric integrated emergency care model may be able to ensure efficient delivery of care to patients experiencing time-sensitive emergencies and advance towards the coveted target under Sustainable Development Goals (SDGs).

**Ethics and dissemination:**

Ethics approval was obtained in all the project sites. The results of the project will be submitted to a peer-reviewed journal for publication, in addition to national and state-level dissemination.

**Trial registration:**

The trial is registered with CTRI (Clinical Trial Registry of India; CTRI/2024/01/061304).

## Introduction

India is committed to achieving Sustainable Development Goal 3 by 2030, which aims to “ensure healthy lives and promote well-being for all at all ages,” wherein emergency care systems are pivotal for addressing universal health coverage, road safety, maternal and child health, and various disease burdens. The World Health Organization (WHO) underscores that the absence of timely emergency care significantly contributes to public health crises, with the 72nd World Health Assembly highlighting timeliness as a critical dimension of care quality [1]. The World Bank Disease Control Priorities Project estimates that a high-quality integrated emergency care system could address over half of deaths and a third of disabilities in low- and middle-income countries (LMICs) [2].

Population-level incidence data for emergency medical diseases (EMDs) are scarce; consequently, mortality data are predominantly used to estimate their burden. Globally, emergency EMDs contribute significantly to health burdens, accounting for approximately 28.3 million deaths annually and disproportionately impacting low-income countries. South-East Asia bears a notably high burden, with 90% of deaths and 84% of disability-adjusted life years (DALYs) attributable to emergency conditions. Improved emergency care systems can notably reduce mortality from cardiovascular diseases, neonatal conditions, and maternal conditions. Ischemic heart disease, stroke, neonatal conditions, lower respiratory infections, and a combined category of injuries and road traffic accidents were five leading EMD causes of death in India in 2019 [3]. The combined EDMR of these EMDs was 251 deaths per 100 000 population (111, 51, 32, 29 and 28.3/100,000 population respectively) in all age groups [4,5]. These EMDS were thus responsible for 37.4% of all the deaths in the country. The country also has the highest absolute number of deaths (51,000) due to snakebite in the world (4/100,000 population) [6]. India with a maternal mortality rate of 6/100,000 in the age group of 15–45 years accounts for 12% of the global deaths [7,8]. The leading cause of these maternal deaths were obstetrics haemorrhage (47%) and hypertensive disorders of pregnancy-eclampsia and preeclampsia (7%) in 2019 [9,10]. In view of this, we plan to target time-sensitive emergencies STEMI, stroke, trauma and burns, acute respiratory illness, postpartum haemorrhage and preeclampsia, neonatal emergencies, snake bite and poisoning for building an integrated emergency care model.

India’s emergency care system, while evolving, confronts several deeply entrenched challenges. The Government of India’s public policy think tank, NITI Aayog’s 2021 country level assessment of emergency care delivery brought out various observations. A primary issue is its fragmented nature, leading to a disjointed care continuum from pre-hospital settings through primary, secondary, and tertiary facilities [3]. This fragmentation manifests in multiple uncoordinated initiatives, often establishing separate specialized centers (e.g., for trauma, burns, pediatrics) which can lead to resource duplication without proportional returns on investment. Pre-hospital care is rudimentary, with ambulance systems often suffering from poor infrastructure, a lack of trained personnel, inadequate access, and systemic fragmentation, despite the expansion of services like Dial 102/108 [3,11,12]. Pre-arrival notification to receiving hospitals is often lacking [3]. Further challenges include significant gaps in healthcare infrastructure, workforce shortages, and inequitable distribution of medical provisions, particularly outside tertiary centers [3]. Limited community access to timely care, poor coordination between health facilities, a scarcity of standardized training resources, and low public awareness regarding emergency responses exacerbate the problem. Most emergency services are concentrated at the tertiary level, leaving prehospital, primary, and secondary care systems with limited capabilities. Additionally, there is an absence of robust public-private partnerships, and many attempts to address these issues have been system-focused rather than patient-focused, failing to bridge critical gaps in care delivery and effectiveness.

To address these multifaceted gaps, there is an urgent imperative to develop and implement an integrated emergency care system model. Such a model would aim to manage time-sensitive emergencies more effectively by establishing a seamless continuum of services across different healthcare facilities, interconnected through robust communication, transportation, and referral systems. However, large-scale implementation research employing an integrated approach to develop a scalable, patient-centric emergency care system has not been done in India. Using an implementation research framework the project aims to understand the contextual factors that facilitate or hinder the transition to high-quality emergency systems, providing evidence-based guidance for policymakers and planners for resource allocation, program development, and scaling up successful models nationally and globally. This approach will move beyond system-focused fixes to create a truly patient-centric emergency response framework.

### Aim and objectives

The aim of this study is ‘to develop a scalable model to achieve 80% population coverage with high-quality patient-centric integrated emergency care system in the selected districts of India’ with specific objective to:

Co-develop a district-level implementation model for high-quality patient-centric integrated emergency care through iterative processes.Evaluate the model in terms of feasibility, acceptability, cost, and effectiveness of the implementation to achieve emergency care preparedness and coverage.

## Materials and methods

### Study population and sites

Five districts (Ludhiana, Vadodara, Vidisha, Puri and Puducherry) from 5 Indian States/UTs (Punjab, Gujarat, Madhya Pradesh, Odisha and Puducherry) will be participating in this study. The districts are geographically diverse, have a varied health index, healthcare infrastructure, diverse emergency care challenges, incidence rates and innovative practices (Fig 1). The selected districts are a purposive sample of districts that attempts to be representative of the cross section while ensuring support from state health departments and access to research teams.

### Study design and overview

We plan to conduct a multi-district implementation study using a mixed-methods design that combines formative and evaluation components through three iterative improvement cycles to develop and implement a high-quality emergency care system. Our model will provide quality care to patients with STEMI, stroke, trauma and burns, acute respiratory illness, postpartum haemorrhage and preeclampsia, neonatal emergencies, snake bite and poisoning. The study will be of a three year duration. It will be conducted in collaboration with the state health department.

The study will start with (1) Identification of gaps related to emergency care at pre-hospital, public and private healthcare system; (2) Simultaneously, a community based survey will be done to obtain baseline data on load of EMDs and level of community awareness; (3) Formative research will be done to co-develop a district specific provisional patient centric integrated model of emergency care; (4) optimization of the model through three cycles of iterative processes to provide continuum of care across different levels of the health system; 5. Implementation of the model through hub (tertiary care hospitals) and spokes (a cluster of public health facilities- DH, CHC, PHC) linked via pre-hospital system in a designated geographical area in the district and 6. Evaluation of the model for feasibility, acceptability, cost, effectiveness and coverage in the above five selected districts. It will then be scaled up to the entire district in consultation with the respective state governments and its impact on population coverage will be evaluated (Fig 2). The study results will be disseminated to policy makers at state and national level.

**Fig 2 pone.0331290.g002:**
[figure not shown]
Overview of the study.

### Study stakeholders

(a) Patients who have experienced an emergency condition within the study geography during the study period and have visited a health facility,(b) Community or households, caregiver of patients,(c) Local political leaders (including Panchayats and Block Development Officers), village self-help groups, RWAs, civil society members,(d)Potential first responders: Road safety authority (including traffic police), ambulance drivers and paramedics community groups, taxi and auto drivers, shopkeepers, bystanders, family members etc.,(e) Health care providers and managers: Staff and administration of health facilities, including both public and private sector,(f) Health policy makers and health system management involved in the management and decision-making processes of the emergency care system, e.g., Secretary Health, Mission Director- National Health Mission, Directorate of Health Services, public health and medical education, nodal officer trauma and emergency care, any other key personnel as identified by the State), National Health Authority, regulators, and legal advisors.

### Study team

The study team consists of (a) the research team and (b) the implementation team. These teams will co-develop the district-level emergency care model.

*Research team*: This comprises researchers, state and national health department officials and ICMR. The research team will be primarily responsible for formative research, supporting the implementation of the intervention, and performing data collection for iterative program learning and quality improvement, and assessment of the outcomes. The research team is further divided into three individual teams i) the formative research and program learning team; ii) the implementation support team; iii) the outcome measurement team.

*Implementation team*: This comprises policymakers and administrators at district, state, national level governments, public health care providers and managers, private healthcare facilities and providers, ambulance providers, non-governmental organisations, civil society, non-health departments like transport, education, and communication. The implementation team will be primarily responsible for implementation of the provisional and final model at the district level.

The research team and implementation team will co-develop district level emergency care model. Key roles, staff involved, and key activities of the study team are outlined in Table 1

**Table 1 pone.0331290.t001:** Description of study teams.

Teams	Implementation Team(Government and Private partners)	Research Team (Principal investigators, co-investigators, state health officials, research staff recruited under the study, scientist at ICMR, project steering group and technical advisory group)		
**Overall role**	Co- develop the provisional model Implementation of the provisional and final model	Conduct formative research, co-develop the intervention, support the implementation of the intervention, perform data collection for iterative program learning and quality improvement, and assessment of the outcomes		
**Staff/ Stakeholders**	Policymakers and administrators in the state governments, district health administration, health care providers and managers at district level, private healthcare facilities and providers, ambulance providers, non-governmental organizations, civil society, non-health departments like transport mass media communication and education.	**Formative research and programme learning team**	**Implementation support team**	**Outcome measurement team**
**Activities**	Providing overall leadership and governance. Co-develop the provisional and final model. Create an enabling environment and provide managerial and administrative support for implementation, scale up, and institutionalizationon of the interventions. Implement activities related to the provisional and final model. Provide resources required for effective implementation of the model	Perform formative research to co-develop the provisional model. Qualitative data collection at regular intervals for program learning, reiterations, and continuous quality improvement. Contribute to refinement and optimization of the model	Support the implementation team in health facility preparedness for providing high-quality emergency care. Contribute to refinement and optimization of the model Provide support to the implementation team to implement the provisional models and the final model.	This team will be independent from the formative research team and the implementation support team. Quantitative data collection for concurrent and end evaluation for emergency care preparedness and coverage. Contribute to refinement and optimization of the model

### Formative research

The objective of this phase is to conduct a situational analysis to understand the current state of emergency care systems in the study geography, with the aim of identifying the factors that act as potential barriers and facilitators. This will help in identifying the means to transform the existing system to a high-quality integrated emergency care system.

Though integrated emergency care systems are considered a solution for providing accessibility to emergency care in diverse geographical settings, evidence based information for planning and implementing a patient centric integrated emergency care system, particularly in low resource settings, is required. Therefore, in the initial phase of the study we plan to conduct:(i) a systematic literature review: to synthesise evidence for an integrated emergency care system, which has been adopted globally or within India to meet the needs of the population served. This will provide an overview of what has been tried to be integrated and its purpose; how this can be used to develop the model, processes, strategies and structure within the context of the needs of the population of selected districts. (ii) health system readiness: a. health facility and pre-hospital (ambulance and helpline centres) resource and infrastructure assessment in the study district and a defined area in adjoining districts; b. Mapping of emergency care system: geo spatial mapping of facilities; mapping of current emergency care pathways, care processes and referral pathways using observation checklists, direct observation, and interview with health care providers; c. competency assessment of care providers and 1^st^ responders to assess the knowledge and skills of healthcare providers; d. budgetary provisions abstracted from administrative data including public and private insurance systems and; e. indicators of the current state of emergency care, e.g., hospital emergency visits, types of emergencies, patient outcomes.(iii) A community-based household survey: to estimate the burden of EMDs in the community and assess the health care services sought after the event. The survey data will provide information on the proportion who sought care, pathway of care & referral pathway, delay in seeking care, the expenditure incurred during care provision for the emergency medical condition and utilisation of insurance services. A multistage sampling strategy will be adopted. The study population will be stratified into urban and rural areas. Villages will be the primary sampling unit (PSU) in rural areas. Villages with a population of less than 500 will be excluded from the sampling frame, and villages with a population of more than 5000 will be split into clusters to have an approximate population of around 2000 in each cluster. In an urban area, census enumeration blocks will be a PSU. Sample size is calculated to estimate the burden of emergency medical conditions. Considering the burden of emergency conditions as 141/10000 population (Table 2), assuming a confidence level of 95% and a relative precision of 25% and design effect of one (design effect is considered as one as due to rarity of outcome the events are less likely to be clustered), the required sample size is 4292. Considering a non-response rate of 20% the sample size comes out to be 5365 which is further rounded off to 6000. A total of 60 PSUs will be randomly selected (PSU stratification for urban and rural will be based on district’s urban:rural distribution) and 100 households will be randomly selected from each PSU. All the individuals in the selected household will be included for the purpose of data collection.

**Table 2 pone.0331290.t002:** Burden of emergency conditions.

Baseline coverage (%)	End line coverage (%)	Number required who had an emergency medical condition	Population to be surveyed
10	20	216	16241
	30	69	5188
	40	36	2707
20	30	311	23383
	40	89	6692
	50	43	3233
30	40	373	28045
	50	101	7594
	60	46	3759
40	50	405	30451
	60	104	7820
	70	46	3459
	80	25	1880

The qualitative component of the formative research will involve semi-structured interviews, focus groups, and surveys with key stakeholders, including administrators, policymakers, healthcare providers, first responders, paramedics, community groups, and patients. These interactions aim to gather diverse perspectives on state and district-level policymaking, program implementation, and financing options. Additionally, experiences and best practices from existing state-led programs like TAEI in Tamil Nadu and ambulance systems in Gujarat and STEMI and stroke models in Ludhiana will be explored [14–16]. Components of formative research, stakeholders, data collection techniques and sample size for each activity is provided in S1 Table.

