### Scaling up of the final model

The piloted final model ‘Px’ will be scaled up step-wise to the entire district in a phased manner. The scaling-up sequence will start from the hub and spoke system where pilot testing was conducted and then progressively moved to the other spokes and other hubs of the district. A detailed scale-up strategy, tools to be used for scale-up and scalability of the model will be co-developed by consultation with the state. The objective during this phase is to implement the final high-quality integrated INDIA-EMS model across the whole district to achieve 80% population coverage of this model. This rollout will be done primarily by the district administration (the implementation team), with support from the program learning team. The outcome assessment team will conduct the concurrent evaluation and the endline population survey.

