Evaluation will be done at baseline, concurrently during the implementation of the model and at the endline(S5 Table). Baseline, concurrent evaluations, and end-line survey data will be analysed to assess the feasibility, acceptability and the cost of the implementation of the model, and the effectiveness of the implemented model in terms of emergency care preparedness and coverage. Concurrent evaluation: Health facility assessment, qualitative interview with stakeholders, competency assessment of care providers will be done concurrently at an interval of three months. Post-care interviews (telephonically) of patients will be done to assess coverage and timeliness of care, expenditure, pathway of care, and delay in care. Endline evaluation: Endline survey will be conducted after the completion of the implementation phase. The sampling strategy and methodology of the endline survey will be similar to the baseline survey. Objective of the endline survey will be to estimate the increase in population coverage and health facility preparedness as compared to the baseline. The estimate of population coverage (i.e., reaching the appropriate health facility within a specified time frame as per the condition; this time frame will be decided during the formative research) obtained during the baseline survey will be used to calculate the sample size for the endline survey. Thus, the sample size for the endline survey will be calculated after the analysis of the results of the baseline survey. We are providing an illustration for sample size required for different scenarios of population coverage assuming a power of 80%, the confidence level of 95%, and a non-response rate of 20%. Thus, sample size included in baseline survey (at the district level) will be sufficient if there is at least 20% increase in population coverage from pre-intervention to post-intervention.

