#### Quantitative analysis.

The data will be duly checked for duplication, redundancies, missing values, and outliers. The key variables will be identified and summarized by measure of central tendency and measure of dispersion as per variable type. The incidence of emergency medical conditions will be calculated separately for urban and rural areas and pooled weighted estimates will be calculated based on distribution of population in urban and rural areas. The effect of the implementation model will be assessed statistically using appropriate methods as described here; We will perform the repeated measure Analysis of variance (ANOVA) as a univariate analysis for those dependent variables which are continuous in nature and having a within-subject correlation. The multivariate analysis for the same variables will be performed by linear mixed effect models (to account for population level and individual level variability). We further propose to calculate a population-average effect by Generalized Estimating Equations (GEE) looking at the structure of the data collection plan and robustness of GEE in the case of model misspecification. The temporal pattern (if any) in some variables will be checked by autoregressive integrated moving average (ARIMA) and if any temporal pattern is indicated we will perform a time-to-event analysis using Cox proportional hazard model.

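### The household survey leaves out villages under 500 people while the 80% coverage target is set for the whole district, so the surveyed population is narrower than the target population and nothing in the plan corrects for it

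*Protocol article*

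**What the plan says.** Under Formative research, the rural primary sampling units (PSUs) of the community survey are villages. The rule at the lower end is: "Villages with a population of less than 500 will be excluded from the sampling frame". At the upper end, villages above 5000 people are split into clusters of about 2000. Sixty PSUs are drawn, with 100 households in each. No reason for the lower cut-off is given, and no figure for the population it removes.

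The endline survey inherits the rule (evaluation paragraph under Secondary outcomes): "The sampling strategy and methodology of the endline survey will be similar to the baseline survey". Its purpose is to "estimate the increase in population coverage and health facility preparedness as compared to the baseline".

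The target carries no matching restriction. The aim is "to develop a scalable model to achieve 80% population coverage with high-quality patient-centric integrated emergency care system in the selected districts of India". The scale-up section wants to "implement the final high-quality integrated INDIA-EMS model across the whole district to achieve 80% population coverage of this model". Evaluation of the India-EMS model repeats the 80% for the district.

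The only weighting described is in Quantitative analysis, for incidence: "pooled weighted estimates will be calculated based on distribution of population in urban and rural areas".

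**The concern.** Residents of villages under 500 people have zero probability of selection at both surveys, but they belong to the population for which 80% coverage is to be claimed. Two features of the plan might seem to help, and neither does. The urban/rural weighting restores the balance between the two strata but cannot represent villages that were never sampled; if the rural weight uses the total rural population, it simply passes the excluded villages' share to the larger ones. The telephone post-care interviews reach only patients who were already in care, so they cannot show who in a small village never got there.

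At stake is the coverage level that will be set against a fixed 80% threshold. The outcome is definitive care at an appropriate facility in time, and the Introduction describes inadequate ambulance access, limited community access to timely care, and services concentrated at the tertiary level. It is plausible that the smallest settlements do worse on such an outcome. The burden estimate, the survey's other purpose, rests on the same restricted frame.

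**Working it through.** **The plan's own figure.** The survey sample size uses "Considering the burden of emergency conditions as 141/10000 population", 95% confidence, 25% relative precision and design effect 1:

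n = 1.96² × (1 − 0.0141) / (0.0141 × 0.25²) = 3.8416 × 0.9859 / 0.00088125 ≈ 4298, against 4292 stated (about 0.1% apart). Then 4292 / 0.80 = 5365, as stated, rounded to 6000. The exclusion does not enter this calculation, so the point does not alter the sample size.

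**Bias in the level.** Let f be the share of emergency patients who live in excluded villages (the primary outcome is a proportion of patients, so this is the relevant share), c_in the coverage in framed areas and c_out the coverage in excluded villages.

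- District coverage = (1 − f) × c_in + f × c_out
- Survey estimate minus district value = f × (c_in − c_out)

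The documents give neither f nor the gap. Under assumed values:

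| f (assumed) | gap 10 points | gap 30 points | gap 40 points |
|---|---|---|---|
| 1% | 0.1 | 0.3 | 0.4 |
| 2% | 0.2 | 0.6 | 0.8 |
| 5% | 0.5 | 1.5 | 2.0 |
| 10% | 1.0 | 3.0 | 4.0 |
| 20% | 2.0 | 6.0 | 8.0 |

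The working range is f of 2–10% and a gap of 10–30 points: 0.02 × 10 = 0.2 to 0.10 × 30 = 3.0 points. If there is no gap, the bias is zero; if small villages do better, it is negative.

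**Bounds without assuming a gap.** If the survey shows 80%, the district value lies between (1 − f) × 80 (no coverage in excluded villages) and that figure plus f × 100 (full coverage there):

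- f = 2%: 0.98 × 80 = 78.4 to 78.4 + 2 = 80.4
- f = 10%: 0.90 × 80 = 72.0 to 72.0 + 10 = 82.0

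**Bias in the change.** With the same frame and the same f at both rounds, the bias is f × (gap at endline − gap at baseline). It is zero for a constant gap. At f = 10% it is 0.10 × (40 − 10) = +3.0 points if the gap widens from 10 to 40, and −3.0 points if it narrows from 40 to 10.

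**Scale against sampling error** (95% half-width at 80% coverage, design effect 1, for one district):

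- 6000 read as persons: 6000 × 0.0141 ≈ 85 cases; 1.96 × √(0.8 × 0.2 / 85) ≈ 8.5 points.
- 60 × 100 read as households with all members included, at an assumed 4 persons each: 24,000 × 0.0141 ≈ 338 cases; about 4.3 points. At an assumed 5 persons: 30,000 × 0.0141 = 423 cases; about 3.8 points.

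The 0.2–3.0 point range lies inside each of these half-widths, but unlike sampling error it does not shrink as the sample grows.

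**The case against.** The strongest objection is that harm is not shown. No passage reports coverage, distance or ambulance reach by village size, and a small village may lie close to a town or a facility. This stands. A reader might infer that the survey will overstate coverage; the documents make that plausible and no more.

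Second, the endline survey's stated objective is the increase over baseline, and using the same frame twice removes a constant gap. This also stands. A reader might infer that the measured gain is inflated because larger settlements are served first. The scale-up section orders roll-out from the pilot hub to other spokes and hubs, not by settlement size, and the endline survey follows completion of implementation.

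Third, the cut-off has a visible practical reason, though the article does not state it: at an assumed 5 persons per household, a village under 500 cannot supply 100 households. This explains the rule but does not require losing the population, since joining neighbours meets the same need.

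Fourth, the full protocol may justify the cut-off or give the excluded share. That is possible, and the absence of a justification is not the finding. The finding is that the article itself fixes an exclusion and, without qualification, a whole-district target.

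**Conclusion.** The mismatch is real and stated in the text: the survey frame is narrower than the population of the 80% target at both rounds, and neither the weighting nor the post-care interviews repair it. The coverage level may be biased, plausibly upward. The size is 0.2–3.0 points if the excluded villages hold 2–10% of emergency patients and their coverage is 10–30 points lower. Both inputs are assumptions. At a share near 1% the effect is negligible; at 10–20% it could decide whether 80% is judged as met. The before-after change is affected only if the gap moves, and then in either direction.

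It would go too far to say that the survey can support no statement about district coverage. Once the excluded share is known, the district figure can be bounded, as the working shows. This is an improvement that should be made, not a flaw that invalidates the survey.

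**What to change.** Replace the exclusion with a joining rule: villages under 500 people are combined with adjoining small villages until the unit has at least 500 people, and the unit counts as one PSU. Apply the existing splitting rule for more than 5000 people after joining. This mirrors what the plan already does for large villages and leaves the number of PSUs and households unchanged.

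The study began in January 2024, so baseline fieldwork may be complete. In that case use the combined frame at endline, whose sample size is in any event to be set after the baseline analysis. Make the before-after comparison on the original frame, and judge the 80% level on the full frame.

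In either case, report the excluded population share for each district. If the frame is not changed, state that coverage refers to the framed population and give bounds for the district.

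The cost is some listing work, some extra travel within combined units, and slightly lower precision for the before-after comparison, because endline households in formerly excluded villages do not enter it. If those villages hold 2–10% of endline cases, the standard error of the endline estimate on the original frame rises by a factor of 1/√0.98 ≈ 1.01 to 1/√0.90 ≈ 1.05.
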